## Methods

### Research aim

The aim of this research is to assess the safety (evaluated as rate of hypoglycemia) that this 4-step strategy has on patients with T1D after completing a series of simulated soccer tests. As exploratory analysis, we will compare the performance of the skills required to achieve a good score in the selected test. We will also aim to identify an optimal pre-exercise blood glucose level associated with a better performance in simulated soccer tests. Finally, we will evaluate the effect of this 4-step strategy for blood glucose level control in the cognitive performance (indexed by neuropsychological evaluations testing executive functions, attention, working memory, psychomotor speed, and visual-spatial short-term memory) in patients diagnosed with T1D.

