#### Active intervention: real 4-step method

Participants will come to the laboratory at 7:00 a.m. and we will first obtain a resting, fasted venous blood sample (via venipuncture) for the laboratory evaluations previously listed. The iPro2 Professional continuous glucose monitor (CGM) with Enlite sensor (Medtronic, MN, USA) will be installed at that time. Participants will then consume a standardized cereal-based breakfast meal (sugar-coated corn flakes, peaches, and semi-skimmed milk; 1.3 g carbohydrate · kg^-1^ body mass). At 1:00 p.m. participants will consume a standardized pasta-based lunch meal (pasta, tomato-based sauce, cheddar cheese, olive oil; 1.3 g carbohydrate · kg^-1^ body mass). Between the morning and evening visits, participants will record their self-measured glucose control every 2 h.

At 5:00 p.m. participants will arrive for the evening training session. Before starting this session, they will self-administer a 50% reduced pre-meal rapid-acting insulin dose into the abdomen (the injection site will be at the mid-point between the iliac crest and the navel). Immediately after receiving this insulin dose, participants will consume a pre-exercise carbohydrate bolus (sugar-coated corn flakes, peaches and semi-skimmed milk; 1.0 g carbohydrate · kg^-1^ body mass). Following this bolus, participants will remain rested for 60 min, at which point a finger stick sample for glucose testing will be drawn immediately before starting with the training sessions.

At 60 min post-exercise, participants will self-administer a pre-meal rapid-acting insulin dose reduced by 50%, into the abdominal site contralateral to the previously administered pre-exercise rapid-acting insulin injection. After receiving this insulin dose, participants will consume a carbohydrate-based meal (basmati rice, tomato-based sauce, turkey breast, and an isomaltulose orange flavored drink (10% solution); 1.0 g carbohydrate · kg^-1^ body mass) designed to elicit a low GI (GI = 37) response [2].

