### Outcomes

A physician will follow the participants’ blood glucose levels un-blinded, a week before each assessment session. This control will be based on an email report of the daily blood glucose levels 7 days before the training session.

During each of the assessments (visits 3 and 6; see Table 3) a CGM will be installed at 7:00 a.m. and will be maintained until 48 h after the training session ends. During each of these visits the participants will perform the soccer performance evaluation at 5:00 p.m. These training sessions must be separated by 3 weeks, with the idea of reducing a possible “learning effect” associated with repeated workouts. In the 48 h following each training session, participants will be required to measure their blood glucose level eight times (i.e., 2 h after dinner, before going to bed, at 12:00 a.m., at 3:00 a.m., just before breakfast, 2 h after breakfast, just before lunch, 2 h after lunch, and just before dinner). They will also be provided with a form where they will be required to register the appearance and timing of symptoms of hypoglycemia. Blood glucose level will be evaluated using the Accu-Chek® Nano Glucometer (Roche Servicios SA, Costa Rica) 30 min before each assessment session, after each one of the workouts, and before both the basal and 24-h cognitive tests.

**Table 3 Tab3:** Study visits summary table

Assessments and interventions	Pre-screening	Visit 1	Visit 2	Visits 3, 6	Visit 5	Visits 4, 7
Review of eligibility criteria	X					
Demographic data and clinical evaluation		X				
BMI measurement and laboratory evaluation		X				
Theoretical and practical explanation of training exercises			X			
4-Step method and usual care recommendations educational sessions			X		X	
Training sessions with simulated soccer exercises (LIST-P, LSST, LSPT)				X		
Cognitive evaluations				X		X
Efficacy of blinding assessment					X	X
Revision of self-monitoring of blood glucose after exercise session						X
Approximated time	30 min	60 min	90 min	120 min	90 min	60 min

*BMI* body mass index, *LIST-P* Loughborough Intermittent Shuttle Test Prescribed and Self-Paced, *LSST* Loughborough Soccer Shooting Test, *LSPT* Loughborough Soccer Passing Test

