After completing the first evaluation, participants will change their interventional arm, and both groups will receive a second educational session (visit 5) from an endocrinologist, who will explain the details of their new dietary and pharmacological interventions. Also in this visit, we will assess the efficacy of blinding by asking participants in which interventional arm they think they are allocated, and how confident they are about their answer.

Furthermore, participants will be seen the day following each assessment visit (visits 4 and 7) during which cognitive testing and self-monitoring of blood glucose will be repeated. In the last visit (visit 7) we will assess the efficacy of blinding again by asking participants in which interventional arm they think they were allocated, and how confident they are about their answer.

All participants will be instructed to replicate and record their diets (MyFitnessPal App®) and maintain their current insulin regimen, without modifying the dose, injection site, or time of injection for 24 h before each experimental trial day (visits 3 and 6). Participants will also be instructed to maintain similar grades of physical activity during the trial, avoiding strenuous exercise during the previous 48 h and 48 h following the simulated soccer drills.

The assessment sessions will occur on two separate days (separated by 3 weeks) and consist of both cognitive and physical activity evaluations. During the physical activity assessments participants’ heart rate (HR) will be traced with a Garmin Vivofit 2 Bundle with HR monitor (Garmin^©^, Kansas, USA).

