### Statistical methods

In order to evaluate glucose control, we will also compare the two groups, using either Student’s paired *t* test or the Wilcoxon-Mann-Whitney test, in terms of CGM parameters that include: 24-h mean glucose levels, SD of 24-h glucose levels, area under the curve for 24-h glucose, mean amplitude of glycemic excursions, number of episodes of hypoglycemia (<60 mg · dL^-1^), time in hypoglycemia (<60 mg · dL^-1^) during a 24-h period, time in hyperglycemia (>180 mg · dL^-1^) during a 24-h period, and range of postprandial glucose increase. The range of glucose increase (from pre-meal to post-prandial peak levels) after breakfast, lunch, and dinner, will also be compared between the interventional groups, using either repeated measures analysis of variance (ANOVA) or the Kruskal-Wallis test, depending on the normality of the data distribution.

We will assess for data from the LIST-P, LSPT, and LSST, and the Stroop, DVT, DBT, and RVIP test scores obtained for each assessment session, for normality of distribution using histogram analysis, the Shapiro-Wilk test and the Kolmogorov-Smirnov test. We will use a logarithmic transformation for the correction of non-normal data and will subsequently test for the differences between groups using Student’s paired *t* test. In order to assess if the order of the intervention modified the performance of individual participants, we will calculate the difference of the scores obtained between the two types of interventions (real intervention minus sham 4-step method) and then we will define an intervention indicator variable that will take the value of 1 if the subject started with the real 4-step method, and 0 if the subject started with the sham 4-step method. We will then fit a linear regression model with the difference calculated as the response variable and the intervention indicator along with other relevant covariates (age, gender, BMI) as the independent variables. Moreover we will test for time effect over the performance of the participants in a time-varying regression model. Additionally, Pearson correlation coefficients will be calculated between each of the scores and the pre-exercise blood glucose level, searching for linear correlation between blood glucose values and the LIST-P, LSPT, LSST, and Stroop test scores.

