In the event that the data do not follow the normal distribution even after the log-transformation, we will conduct non-parametric analyses using the Wilcoxon-Mann-Whitney test and calculate Spearman correlation coefficients for the comparison between the two groups of the performance scores in soccer and cognitive tests, and for the linear correlation analysis, respectively. A *p* value <0.05 will be considered significant for the comparison of the scores.

Additionally, we will conduct exploratory analyses by modeling the performance scores in soccer evaluations adjusted by age, years since T1D diagnosis, HbA1c level, weekly physical activity hours and Stroop test scores using linear multiple regression. A *p* value <0.10 will be considered significant to introduce a variable into the multivariate regression model. The number of hypoglycemic events and the percentage of other adverse effects listed previously will also be compared among groups using Student’s *t* test and the Fisher exact test, respectively. All of the statistical analysis will be done using Stata software (StataCorp LP® 13.1).

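### The aim is an optimal pre-exercise glucose level, but the only planned analysis is linear or rank correlation, which cannot locate one

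*Protocol article*

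**What the plan says.** The Research aim section of the protocol article states: "We will also aim to identify an optimal pre-exercise blood glucose level associated with a better performance in simulated soccer tests". It stands among the aims that follow the primary safety aim, directly after a sentence that calls the comparison of skills exploratory.

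Statistical methods gives one analysis that links pre-exercise glucose to the scores: "Pearson correlation coefficients will be calculated between each of the scores and the pre-exercise blood glucose level, searching for linear correlation". If the data stay non-normal after log-transformation, the plan will "calculate Spearman correlation coefficients for the comparison between the two groups". That sentence pairs two methods with two tasks, and read as a whole it assigns the Spearman coefficient to the correlation analysis.

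The exploratory regression in the same section consists of "modeling the performance scores in soccer evaluations adjusted by age, years since T1D diagnosis, HbA1c level, weekly physical activity hours and Stroop test scores". Pre-exercise glucose is not on that list. No quadratic, spline or cut-point analysis of glucose appears anywhere.

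On the data structure, Outcomes says "The assessment sessions will occur on two separate days (separated by 3 weeks", so each participant has one session under each regimen. Two pre-exercise samples are described: one "30 min before each assessment session" (Outcomes) and one "immediately before starting with the training sessions" (section on the real 4-step method).

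**The concern.** An optimum is a level with worse performance on both sides of it. A threshold is a level beyond which performance stops improving. Both are features of a curve. A correlation coefficient reduces the relation to one signed number for trend, so it holds no information about where such a level lies.

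This is not detail left to a later analysis plan: the aim and the method are both stated, and they do not fit. Followed as written, the plan would invite two misreadings. A coefficient near zero would be taken as no relation, although a strong optimum can produce it. A clear positive or negative coefficient would be taken as advice that higher, or lower, glucose is better, although it may only reflect where this sample happened to lie relative to the optimum.

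A smaller matter is that nothing says whether the correlation is run per session, per regimen, or on all sessions together.

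**Working it through.** **Figures in the plan.** The plan gives no figure for this aim. The sample size only fixes how many points there are: 24 participants, and 24 × 1.15 = 27.6, rounded up to the stated 28. With two sessions each, 24 participants give 48 session records.

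**1. What r shows when an optimum exists.**
- Assumptions, not in the documents: optimum 150 mg/dL, glucose normal with SD 50, score = -((glucose - 150)/50)², no noise.
- Let d = (sample mean - 150)/50 and z the standardised glucose, so score = -(z + d)². Then the covariance of z and the score is -2d, and the variance of the score is 2 + 4d².
- Hence r = -2d/√(2 + 4d²).

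| Sample mean (mg/dL) | d | r |
|---|---|---|
| 130 | -0.4 | 0.8/√2.64 = +0.49 |
| 150 | 0 | 0.00 |
| 170 | +0.4 | -0.8/√2.64 = -0.49 |
| 190 | +0.8 | -1.6/√4.56 = -0.75 |

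If the curve explains only half of the score variance, each r is multiplied by √0.5 = 0.71, so 0.49 becomes 0.35 and 0.75 becomes 0.53.

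**2. The same question at the trial's size.** Simulation with one point per person, n = 24, and an inverted U explaining 50% of the variance (assumed). There were 40,000 data sets for Pearson and 4,000 for Spearman and the quadratic fit.

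| Optimum relative to mean glucose | Mean Pearson r | Mean Spearman | Pearson p < 0.05 | Quadratic term p < 0.05 |
|---|---|---|---|---|
| At the mean | 0.00 | -0.01 | 22% | 88% |
| 0.5 SD above | 0.39 | 0.35 | 54% | 80% |
| 1 SD above | 0.56 | 0.52 | 83% | 57% |

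In the first row the expected r is zero, yet it is significant in 22% of data sets. In the last row it is usually significant and would be read as higher is better. In no row does Pearson or Spearman give the location.

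**3. The two sessions per person.** Suppose, as one possible reading, that 24 × 2 = 48 records were correlated as if independent.
- The critical |r| is t/√(n - 2 + t²): 0.404 for n = 24 and 0.285 for n = 48.
- With no true relation, pooling multiplies the variance of r by roughly 1 + ρ_g·ρ_s, where ρ_g and ρ_s are the within-person correlations of glucose and score. The actual error is then about 2[1 - Φ(1.96/√(1 + ρ_g·ρ_s))].
- For ρ_g = ρ_s = 0.5: 1.96/√1.25 = 1.753, giving 0.080. For ρ_g = 0.7 and ρ_s = 0.9: 1.96/√1.63 = 1.535, giving 0.125.
- Simulation (40,000 data sets, 24 persons, ρ_s from 0.5 to 0.9) gives about 0.05 at ρ_g = 0, 0.066 to 0.082 at 0.3, 0.080 to 0.106 at 0.5, and 0.095 to 0.127 at 0.7. With 28 persons the largest value is 0.132.
- One correlation per session keeps the error at about 0.05.

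The documents give no within-person correlations, so all these values are assumptions.

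**The case against.** The strongest reply is that this is an exploratory aim, that no treatment comparison rests on it, and that a full analysis plan may say more. Its minor rank is conceded. But the article does name a method for relating glucose to the scores, and that method cannot answer the stated aim.

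The inverted U is also an assumption. The Background section reports one study in adolescents with type 1 diabetes in which low but not high glucose impaired performance, which suggests a rise to a plateau. A rank correlation would partly detect such a rise, but it would not say where the plateau begins. The point therefore does not depend on symmetry, although a forced quadratic vertex would be a poor remedy. The noise-free values of r are upper ends, as the working shows.

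Three stronger readings are tempting but not supported:

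- **That the plan pools 48 records as independent.** Statistical methods does not say so. The phrase "test scores obtained for each assessment session" is written for the normality check and fits separate analyses per session just as well. Only the ambiguity can be raised, and alone it would be missing detail.
- **That the predictor is defined at two conflicting times.** Two samples are collected, but the analysis names one pre-exercise level without saying which sample it is. That is an unstated choice, not a contradiction.
- **That regimen necessarily confounds the correlation.** The regimens differ in the pre-exercise insulin dose, so regimen may act on performance largely through glucose. Adjusting for it could remove informative variation.

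**Conclusion.** The point holds as a mismatch between a stated aim and a stated method: neither Pearson nor Spearman correlation can locate an optimum or a threshold, and the listed regression does not fill the gap. This follows from what the coefficients measure and needs no assumption. The size is illustrative: r from +0.49 to -0.75 for one and the same optimum rests on an assumed noise-free inverted U with the stated centre and SD, and the values shrink with noise.

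The handling of the two sessions is unstated. A type I error of up to about 0.13 applies only if sessions are pooled and both glucose and score are strongly correlated within person.

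The plan should be changed, but the consequence is confined to an exploratory aim. The primary hypoglycemia outcome is not affected.

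**What to change.** For this aim, replace the correlation with an exploratory mixed model for each soccer score:

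- a participant random intercept and a period term;
- pre-exercise glucose as a curved term, for example a restricted cubic spline with 3 knots, which also allows a plateau;
- adjustment for regimen as a sensitivity analysis;
- one named pre-exercise sample that is available in both regimens.

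Report the fitted curve. Only if it turns within the observed glucose range, and in the direction of better performance (a minimum for the timed passing test), give the estimated optimum with a bootstrap interval that resamples participants. Otherwise state that no optimum was identified.

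If this is not wanted, restate the aim as a linear association between pre-exercise glucose and performance, and say how the two sessions enter the correlation.

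The cost is a change of wording and a little more analysis on data already planned. With 24 to 28 participants the interval for any optimum will probably be wide, which is a reason to label the result exploratory.

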The participants will complete three 15-min blocks of the LIST-P punctuated by 4-min resting periods. After having completed the last block of LIST-P, participants will have 5 min of recovery time, and another finger-based capillary glucose sample will be obtained. After this the participants will complete the second round of Loughborough Soccer Passing and Shooting Tests (LSPT) as subsequently described.

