#### Loughborough Soccer Shooting Test (LSST)

The LSST is also a validated test [21] that allows us to evaluate the capacity of a player (in this case our subjects) to score a goal within a simulated soccer gameplay scenario. This particular aspect of the test reproduces real-life conditions of gameplay, thus yielding a more real score of the subject’s performance.

Immediately following completion of the LSPT protocol, the participants will be evaluated with another capillary finger glucose level. After that, the trainer will proceed with the evaluation of the LSST (see Fig. 3).

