**Fig. 5 Fig5:**
[figure not shown]
SPIRIT flow diagram. (A summary of the planned study interventions and assessments)

Stroop testThe Stroop test is a commonly used neuropsychological tool that measures selective attention and mental processing speed among the cognitive functions that could be affected by attentional fatigue [22]. Campbell et al. utilized the Stroop test in a clinical trial that evaluated participants with T1D during physical activity in a sports camp. The investigators found that reading and color recognition ability were susceptible to impairment as a result of hypoglycemia [12].Commercially available Stroop Color and Word Tests (WPS Publish, Alaska, USA) will be used to assess cognitive processing in our participants. Scores will be determined for reading ability, color recognition, and interference; the latter will be used as an index of the subject’s capacity to maintain attention during the interference caused by the color changes in the typed words [23].Stroop testing will take place immediately following each soccer training session and during the morning evaluation at 8:00 a.m. on the next day. Each of these tests will take 2 to 5 min (time limit of 45 s per slide) for the participants to complete. Participants will be asked to complete the test using three slides: (1) read as many colored words as possible in 45 s; (2) name as many colors of a group of “X” letters as possible in 45 seconds; and (3) name the color in which a word is printed (e.g., “blue”, “green”, or “red” ink) and not the word itself, which is a name of a color (e.g., the word “red” printed in blue ink instead of red ink). Naming the color of the word during this “interference” takes longer and is more prone to errors than when the color of the ink matches the word that names the color [16]. Reading, color naming, and interference scores will be converted to *T* scores according to the manual of Golden and Stroop for further analyses.Digit vigilance testThe digit vigilance test (DVT) works as a measure of sustained attention and psychomotor speed. Participants will be asked to cross out a specific target number (6) as quickly as possible, which appears randomly within 59 rows of 35 single digits on two pages. The examiner will observe the subject's performance on the demonstration rows and then on the first five rows of the test to determine whether corrective feedback is required to discourage an inefficient or poorly motivated response style (e.g., going too fast and missing numbers or going too slow and focusing attention on each individual number). Total time and errors of omission will be recorded. For the first (practice) administration, all participants will be asked to complete the standard format (target = 6) [24].Corsi block-tapping taskThe Corsi block-tapping task (CBT) is widely used for the assessment of visual-spatial short-term memory, both in clinical practice and in experimental research settings. Basically, it is a span task and, as such, a visual-spatial analog to the digit span, as an index of verbal short-term memory. The examiner taps a sequence of blocks, which the participant must repeat subsequently in the correct sequential order. By increasing the length of the sequences, the capacity of the visual-spatial short-term memory can be measured [25].The participant will be seated in front of the examiner, who subsequently will tap the cubes starting with a sequence of two blocks. Two trials will be given per block sequence of the same length. If at least one of these is repeated correctly, the next two trials of a sequence of an increased length will be administered. The cubes will be touched with the index finger at a rate of approximately one cube per second (with no pauses between the individual cubes). The participant will have to tap the cube sequences in the same order immediately after the examiner finishes. The sequences will gradually increase in length. The test will be terminated if the participant fails to reproduce two sequences of equal length. Only a completely, correctly repeated sequence will be scored as correct; self-corrections will be permitted.Rapid visual information processing taskThe rapid visual information processing task (RVIP) is a serial detection task used to probe visual sustained attention and working memory processes. The design of the task consists of a stream of single digits (Arabic numerals 1–9) presented at a rate of 100–110 per minute. Participants are required to detect targets comprising a sequence of three consecutive odd or three consecutive even numbers. In a typical paradigm, targets are presented at a rate of four per 30 s. The critical performance variables include the number of correct responses (“hits”), the reaction time for hits, and the number of errors of commission (response in the absence of a target) [26].This RVIP version will be programmed using e-prime (Version 1.1. Psychology Software Tools, Inc., www.pstnet.com). White numbers between 0 and 9 (excluding 1) will appear in the center of a black computer screen. Each number is presented for 600 ms without a time gap between two succeeding numbers. The participant will have to detect three target sequences (“2–4–6”, “3–5–7”, and “4–6–8”) and respond to them (within 1800 ms after the onset of the last number) by pressing the space bar on the keyboard when the last number of a target sequence appears. The three target sequences will be displayed on the screen during the whole session in order to help the participants remember.Each block will be composed of 150 numbers that appear in a pseudo-random and fixed order; four target sequences will be included in 50 numbers. There will be 72 target sequences that appear during the 9-min test session. In order to prevent a sequence effect, six different RVIP versions will be created by varying these six blocks and then balancing them and pseudo-randomly assigning them to the participants. Hits (H), false alarms (FA) and reaction time (RT) will be recorded by the computer. All RTs shorter than or equal to 100 ms will be excluded from further analyses.

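### Stroop scores are to be correlated with pre-exercise glucose, although Stroop is given only after exercise and a glucose reading is already scheduled before each cognitive session

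*Protocol article*

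**What the plan says.** Under Statistical methods, the protocol article says that "Pearson correlation coefficients will be calculated between each of the scores and the pre-exercise blood glucose level", with the purpose of "searching for linear correlation between blood glucose values and the LIST-P, LSPT, LSST, and Stroop test scores". If normality fails even after log transformation, Spearman coefficients replace Pearson. The glucose variable is not changed for any score.

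The aim that calls for a pre-exercise value is under Research aim: "We will also aim to identify an optimal pre-exercise blood glucose level associated with a better performance in simulated soccer tests". The cognitive aim in the same paragraph concerns the effect of the 4-step strategy and mentions no pre-exercise level.

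The Stroop description sets the timing: "Stroop testing will take place immediately following each soccer training session and during the morning evaluation at 8:00 a.m. on the next day". Under Outcomes, glucometer readings are scheduled 30 minutes before each assessment session, and also "after each one of the workouts, and before both the basal and 24-h cognitive tests". Further finger sticks are planned within the soccer session. After the LIST-P, "another finger-based capillary glucose sample will be obtained". After the passing test and before the shooting test, "the participants will be evaluated with another capillary finger glucose level".

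**The concern.** The Stroop test is justified in the article by earlier evidence that hypoglycemia impaired reading and color recognition. The exposure implied by that rationale is glucose around the time of the test. The planned predictor is a value taken before roughly an hour of exercise. For the morning test it also precedes a meal with rapid-acting insulin, a bedtime snack, basal insulin and a night.

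The trial itself acts on glucose in that interval. Table 2 shows that the arms differ in the glycemic index of the post-exercise meal and of the snack, in the post-exercise rapid-acting dose and in the basal dose. None of this can be reflected in a reading taken beforehand.

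The risk is in interpretation. A weak Stroop correlation could be reported as evidence that glucose does not matter for cognition, when the glucose value tested was not the one present during the test. The better-matched reading is collected, but nothing under Statistical methods relates it to any score.

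**Working it through.** **Timing.** Participants arrive at 5:00 p.m., take insulin and a meal, and rest 60 minutes, so the finger stick just before exercise falls at about 6 p.m. From 6 p.m. to 8 a.m. is 14 hours. The other candidate, the reading 30 minutes before the session, is earlier still.

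| Score | Position relative to pre-exercise reading | Closer reading scheduled? |
|---|---|---|
| LSPT no. 1 | directly after it | the pre-exercise reading is itself the closest |
| LSPT no. 2 | after the LIST-P | yes, after the LIST-P |
| LSST no. 2 | after LSPT no. 2 | yes, between LSPT and LSST |
| Stroop, evening | after the whole session | yes, before the cognitive session |
| Stroop, next morning | about 14 h later | yes, before the cognitive session |

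Table 3 places cognitive testing only at visits 3 and 6 and at visits 4 and 7. I therefore take "before both the basal and 24-h cognitive tests" to mean the evening and next-morning sessions.

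**Inputs.** The protocol states no power or expected size for the correlation analysis. The only sample size concerns hypoglycemia: 24, raised to 28 for dropout. With assumed rates of 70% and 30% (base rates are not given), a two-sided 5% level and 80% power:

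n = [1.960 × √(2 × 0.5 × 0.5) + 0.842 × √(0.7 × 0.3 + 0.3 × 0.7)]² / 0.4² = (1.386 + 0.545)² / 0.16 ≈ 23.3, so 24.

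Then 24 × 1.15 = 27.6, so 28. The stated figures are reproduced. They serve here only to fix n.

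Two quantities are assumptions, because the documents give neither:
- r_true, the correlation of a Stroop score with glucose at the time of the test. I use 0.5, with 0.3 and 0.6 as alternatives.
- ρ, the correlation between pre-exercise glucose and glucose at the time of the test. I use 0.2 to 1.

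**Attenuation.** If pre-exercise glucose bears on the score only through glucose at the time of the test, and relations are linear, r_planned = r_true × ρ.

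**Power.** Fisher z, two-sided 5%, one pair of values per participant: power = Φ(atanh(r)·√(n − 3) − 1.96) + Φ(−atanh(r)·√(n − 3) − 1.96).

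Worked case, r = 0.5 and n = 24: atanh(0.5) = 0.549 and √21 = 4.583, with product 2.517. Φ(2.517 − 1.96) = Φ(0.557) = 0.71.

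| ρ | r_planned if r_true = 0.5 | Power, n = 24 | Power, n = 28 |
|---|---|---|---|
| 1 (test-time glucose) | 0.50 | 71% | 78% |
| 0.8 | 0.40 | 49% | 56% |
| 0.6 | 0.30 | 29% | 34% |
| 0.4 | 0.20 | 15% | 17% |
| 0.2 | 0.10 | 7.5% | 7.9% |

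**Sensitivity to r_true, n = 24.** With r_true = 0.3, power is 29% at ρ = 1 and 13% at ρ = 0.6. With r_true = 0.6, it is 89% and 41%.

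**Smallest detectable correlation at 80% power.** tanh[(1.960 + 0.842)/√(n − 3)] = 0.545 for n = 24 and 0.508 for n = 28. There is no reserve of power to absorb attenuation.

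**The case against.** **Pre-exercise glucose is a declared exposure.** This stands for LIST-P, LSPT and LSST. A reader might infer that every correlation in the list uses the wrong glucose value. The Research aim does not support that, because it asks specifically about pre-exercise level and soccer performance. For LSPT no. 1 the pre-exercise reading is also the one nearest the test. The aim does not extend to Stroop.

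**The morning Stroop may not be in the analysis.** Statistical methods speaks of scores from each assessment session, and the morning visit is the day after that session. So it is not certain that the 14-hour case applies. The article does not say which Stroop time point is used. The point survives either way, since both Stroop tests follow exercise and both have their own reading.

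**The size is assumed.** This stands. A reader might infer that the planned correlation is diluted to near zero. That would need ρ of about 0.2 or less, which is plausible for the morning test but not shown. For the evening test ρ could be much higher. Nor is r_true = 0.5 guaranteed with better-matched glucose: the Background cites a study in which low but not high glucose impaired performance, so the relation may not be linear.

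**The cognitive aim is met elsewhere.** Also correct. The effect of the 4-step method on cognition is tested by the paired comparison of arms, which does not depend on this correlation. The finger-stick values also have other uses: the Data collection section checks them against the recordings. What is missing is only a link between these readings and the Stroop scores.

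**Conclusion.** The concern holds for Stroop. The article fixes pre-exercise glucose as the predictor of a test given only after exercise. No stated aim asks for that predictor, and a reading before each cognitive session is already scheduled. The correlation would be reduced by the factor ρ, which is unknown. With r_true = 0.5 and 24 participants, power falls from 71% to between 49% and 7.5% as ρ goes from 0.8 to 0.2. These figures assume linearity, action only through test-time glucose, and one pair per participant. Using both sessions of each participant would need a method for repeated measures.

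It does not follow that the soccer correlations are wrong, that the Stroop correlation must be close to zero, or that the trial cannot assess cognition. The analysis is exploratory and bears on neither the primary outcome nor the comparison of arms. The practical consequence is that a null Stroop correlation, as planned, would say little about the effect of glucose on cognition.

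**What to change.** In Statistical methods, state that each Stroop score, post-session and next morning, is correlated with the finger-stick glucose taken before that cognitive session. State which Stroop time points are analyzed, and confirm that the basal cognitive test named under Outcomes is the post-session one. Keep pre-exercise glucose as the predictor for the soccer tests, in line with the Research aim.

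As an optional supplement, correlate LSPT no. 2 with the reading after the LIST-P, and LSST no. 2 with the reading between the passing and shooting tests.

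The cost is a change of analysis wording. No visit, sample or test is added, because these readings are already scheduled.
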